** *Religious Norm Violation #1* **					
*Item*	This is a [woman/man] named [character]. [Character] is Christian. [Character] never goes to church. [She/He] could, but [she/he] chooses not to.	This is a [woman/man] named [character]. [Character] is Catholic. [Character] never goes to church. [She/He] could, but [she/he] chooses not to.	This is a [woman/man] named [character]. [Character] is a member of the Church of Jesus Christ. [Character] never gives money to the church.	This is a [woman/man] named [character]. [Character] is Jewish. [Character] never lights candles on Friday nights.	This is a [woman/man] named [character]. [Character] is Muslim. [Character] never does [her/his] five daily prayers.
*Character*, *ingroup*	Christina/Mark	Christina/Mark	Christina/Mark	Rebecca/David	Yara/Danny
*Character*, *non-ingroup*	Jesse	Jesse	Jesse	Jesse	Jesse
** *Religious Norm Violation #2* **					
*Item*	This is a [woman/man] named [character]. [Character] is Christian. [Character] was never baptized—so a priest or pastor never put water on [her/his] head.	This is a [woman/man] named [character]. [Character] is Catholic. [Character] was never baptized—so a priest or pastor never put water on [her/his] head.	This is a [woman/man] named [character]. [Character] is a member of the Church of Jesus Christ. [Character] drinks coffee.	This is a [woman/man] named [character]. [Character] is Jewish. [Character] eats foods that are not kosher.	This is a [woman/man] named [character]. [Character] is Muslim. [Character] eats foods that are not halal.
*Character*, *ingroup*	Natalie/Luke	Natalie/Luke	Natalie/Luke	Rachel/Adam	Yasmina/Rami
*Character*, *non-ingroup*	Morgan	Morgan	Morgan	Morgan	Morgan
** *Moral Norm Violation* **					
*Item*	This is a [woman/man] named [character]. [Character] is Christian. [Character] hits other people for no reason.	This is a [woman/man] named [character]. [Character] is Catholic. [Character] hits other people for no reason.	This is a [woman/man] named [character]. [Character] is a member of the Church of Jesus Christ. [Character] hits other people for no reason.	This is a [woman/man] named [character]. [Character] is Jewish. [Character] hits other people for no reason.	This is a [woman/man] named [character]. [Character] is Muslim. [Character] hits other people for no reason.
*Character*, *ingroup*	Mary/Chris	Mary/Chris	Mary/Chris	Leah/Michael	Mona/Kareem
*Character*, *non-ingroup*	Jordan	Jordan	Jordan	Jordan	Jordan
** *Conventional Norm Violation* **					
*Item*	This is a [woman/man] named [character]. [Character] is Christian. [Character] wears socks on [his/her] hands.	This is a [woman/man] named [character]. [Character] is Catholic. [Character] wears socks on [his/her] hands.	This is a [woman/man] named [character]. [Character] is a member of the Church of Jesus Christ. [Character] wears socks on [his/her] hands.	This is a [woman/man] named [character]. [Character] is Jewish. [Character] wears socks on [his/her] hands.	This is a [woman/man] named [character]. [Character] is Muslim. [Character] wears socks on [his/her] hands.
*Character*, *ingroup*	Grace/Matthew	Grace/Matthew	Grace/Matthew	Sarah/Samuel	Leila/Nidal
*Character*, *non-ingroup*	Riley	Riley	Riley	Riley	Riley
** *Religious authority* **					
	God	God	God	God^a^	Allah
** *Familiarity assessment* **					
*Reference religious group*	Christians	Catholics	members of the Church of Jesus Christ	Jews	Muslims
*Norm #1*	going to church	going to church	giving money to church	eating food that is kosher	eating food that is halal
*Norm #2*	getting baptized	getting baptized	not drinking coffee	lighting candles on Friday night	praying five daily prayers

Unaffiliated children in the US are shown the version of the protocol that corresponds to the religion with which they are likely most familiar (see main text for details). See main text for descriptions of network-wide guidelines for item selection. “L.D.S.” stands for “Latter-day Saints.”

^a^ If the researcher becomes aware that the child is more familiar with the term “Hashem” or “Adonai” then the more familiar term is used in place of “God” throughout the Child Protocol.

After completing all four blocks of questions, the child is asked a series of questions intended to gauge awareness of religious norms in general and familiarity with the two religious norms featured in this task. First, the researcher asks the child, “Are there any rules that [target religious group members] should follow? Like anything they are supposed to do, or not supposed to do?” If the child does not provide a meaningful response, the researcher follows up with, “What are things that only people who go to the same [house of worship] as you do, or do not do?” Then, the researcher asks the child directly about each of the two religious norms featured in this task, by asking, “What about [target religious group members] [following the religious norm]?–is that something you have heard of?” If the child has already mentioned one or both of the religious norms in the initial open-ended question, the researcher skips the corresponding follow-up question(s).

Across the four blocks, we include two religious norms, one moral norm, and one conventional norm.

The two *religious* norms featured in this task conform to the following network-wide guidelines. First, all religious norm violations are transgressions of injunctive religious norms (i.e., violations of rules explicitly laid out by a religious authority) rather than transgressions of religious norms that might also be considered “moral” (e.g., being kind to others) or “conventional” (e.g., taking off shoes before entering someone’s home). Second, all religious norms are intended to distinguish the target religious group from other world religions and other high-level religious groups in the local context; for example, for a version of the protocol designed for Muslim participants who also encounter Christians, both religious norms are required to pick out rules that Muslims abide by but Christians do not. (Religious norms are allowed but *not* required to distinguish sub-groups within an overarching religion, e.g., Sunni vs. Shia; Catholic vs. Protestant.) Third, religious norms are required to be salient and familiar to children, as confirmed by local informants (e.g., religious leaders, parents of young children); however, they are not required to be applicable to children themselves, i.e., they might focus on behaviors that are only required of adults.

Within these guidelines, the religious norms featured in this task are designed to vary across samples in order to preserve cultural and religious specificity and appropriateness. First, across samples, most religious norms apply equally to all genders, but some are gender-specific (e.g., applying only to women, or applying differently to men and women). If the norm is gender-specific, the gender of the character is fixed to be the relevant gender (regardless of the participating child’s gender); otherwise, the gender of the character is matched to the participant’s gender (or fixed to be a woman if the participating child does not identify as a boy or a girl, or if the participating child’s gender is unknown). Second, across samples, some religious norms are prescriptive (i.e., outlining a behavior that a person should do), while others are proscriptive (outlining a behavior that a person should not do). Third, across samples, religious norms cover a wide range of religious content, including but not limited to rules surrounding eating, prayer, dress, and ritual.

In contrast to the variability present among the religious norms featured in this task, the moral and conventional norms are standardized across samples. The *moral* norm is “[Character] hits other people for no reason”: an obvious and familiar violation of the common moral injunction against unjustified harm to others. The *conventional* norm violation is “[Character] wears socks on [his/her] hands” (or some close variant): an obvious violation of common rules about how clothing is intended to be worn and is typically worn. Research teams agreed these norms were relevant in all planned samples at the time of the design of the study protocol.

Depending on the sampling plans in place at a given field site, the target religious group featured in this task corresponds either to the participating child’s own religious group membership, to a religious group with which the child’s parent has indicated that they are familiar, or to a religious group that is prevalent in the participating child’s local context. The target religious group featured in this task is matched to the religious “target group” or “reference group” featured in the Sorting, Religious Indicators, Social Essentialism, and Child as Transmission Agent tasks (described in other sections). The names of characters are consistent with the religious group membership or non-membership described in the stories (e.g., the name “Jesús” would be acceptable for a character who is described as “Christian,” but not for a character who is described as “Jewish” or as “not Christian”).

With the exception of gender-specific religious norms (described above), the gender of the characters featured in this task are matched to the participating child’s gender; if the participating child does not identify as a boy or a girl, or if the participating child’s gender is unknown, the child is shown the “girl” version of the task.

In the US samples, this task is estimated to take 7 to 14 minutes with younger participants and 7 to 11 minutes with the oldest participants.

*Adaptation for US samples*. The final set of properties featured in the Norm Violations task for the five religions included in US samples is presented in Table 5.

*Parallel tasks with parents/caregivers*. All parents/caregivers are asked two open-ended questions designed to elicit salient religious norms for children in these settings. Parents/caregivers are first told, “Now we have some questions about religious rules. Most religions in the world have rules about being kind to others and staying pure. In addition, many religions have other rules that people are expected to follow as part of their faith. For example, in some religions, people are required to wear particular clothing (either all of the time or under certain circumstances), to eat or to avoid eating certain foods, to pray in particular ways or at particular times, or to change their behavior during certain holidays.” Then they are asked to provide open-ended responses to the following two questions: (1) “Of these kinds of rules, what ones do you focus on most with your child?” and (2) “Why should your children follow these rules?”

In some samples, including all US samples, parents/caregivers are also asked to complete a task parallel to the Norm Violations just described. Following the open-ended questions described above, parents/caregivers proceed directly to the permissibility and severity assessments of the two religious norms that their child has assessed, with the gender of the characters matched to the participating child’s gender. Parents/caregivers assess only the two religious norms and provide only permissibility and severity judgments about a norm violation committed by a member of the target religious group. After the permissibility and severity assessments, parents/caregivers are also asked about how they would feel and what they would do if their own child violated the norm in question. Parents/caregivers complete all questions about the first religious norm before proceeding to the next religious norm, and norms are presented in a fixed order for all parents/caregivers within a sample.

*Planned analyses*. The main contribution of the data on norms will be the cross-cultural examination of how children develop conceptions of religious norms. As part of this examination, we also seek to compare children’s conceptions of religious norms to their conceptions of moral norms against the harming of others and conventional norms about how to dress.

First, with respect to children’s distinctions between religious and moral norms, we hypothesize that children will (1a) deem moral violations less permissible and more severely negative than religious violations, (1b) provide religious justifications more often when explaining judgments about religious norm violations and refer to victim welfare more often when explaining judgments about moral violations, (1c) be more likely to judge that religious norms are alterable by religious authorities than to judge that moral norms are alterable by religious authorities, and (1d) be more likely to apply moral norms to characters who are not members of the target religion than to apply religious norms to members of the target religion. (For previous work that has informed these hypotheses, see [70, 72–78].)

Second, with respect to children’s distinctions between religious and conventional norms, we predict that children will (2a) provide religious justifications more often when explaining judgments about religious norm violations and refer to secular authorities (e.g., teachers, parents) more often when explaining judgments about conventional violations, and (2b) be more likely to apply conventional norms to characters who are not members of the target religion than to apply religious norms to members of the target religion. (See [70, 72–78].)

To test these hypotheses, we will examine the main effects of norm type (religious vs. moral, religious vs. conventional) on children’s initial permissibility and severity ratings (relevant to hypothesis 1a); their open-ended justifications of their permissibility ratings (relevant to hypotheses 1b and 2a); their permissibility and severity ratings in the “alterability” portion of the block (relevant to hypothesis 1c); and their final permissibility and severity ratings for characters who are not members of the target religion (relevant to hypotheses 1d and 2b). For predictions about alterability and scope (hypotheses 1c, 1d, and 2b), we will also examine the main effect of norm type on the *differences* between children’s initial and later responses, i.e., compare children’s permissibility and severity ratings for characters who are not members of the target religion to their own initial permissibility and severity ratings for members of the target religion.

Of central interest will be differences in children’s responses across age and across samples from different cultural-religious groups; these analyses will be exploratory and will likely hinge on modifying the analyses just described to include statistical interactions with age and/or sample.

Beyond these predictions, we plan to conduct item-level analyses (e.g., examining relationships and comparisons across the permissibility, severity, alterability, and scope questions for each of the individual norms included in the study, or examining norm type differences considering each of these questions separately); to compare children’s responses to those of parents/caregivers; to explore relationships between children’s responses in this task and information provided in the Parent Survey; and to examine relationships between this and other tasks included in the Child Protocol.

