** *Belief* **					
*Religious*	Here’s a kid who believes that Jesus died for our sins.	Here’s a kid who believes that Jesus died for our sins.	Here’s a kid who believes that Joseph Smith was God’s prophet.	Here’s a kid who believes that God sent ten plagues.	Here’s a kid who believes that the Prophet Muhammad is Allah’s messenger.
*Neutral*	Here’s a kid who believes that George Washington was a US president.	Here’s a kid who believes that George Washington was a US president.	Here’s a kid who believes that George Washington was a US president.	Here’s a kid who believes that George Washington was a US president.	Here’s a kid who believes that George Washington was a US president.

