** *Holiday* **					
*Religious*	Here’s a kid who goes to church on Easter.	Here’s a kid who goes to mass on Ash Wednesday.	Here’s a kid who goes to church on Pioneer Day.	Here’s a kid who visits the temple or synagogue during Hanukkah.	Here’s a kid who celebrates Eid Al Fitr.
*Neutral*	Here’s a kid who gives out valentines on Valentine’s Day.	Here’s a kid who gives out valentines on Valentine’s Day.	Here’s a kid who gives out valentines on Valentine’s Day.	Here’s a kid who gives out valentines on Valentine’s Day.	Here’s a kid who gives out valentines on Valentine’s Day.

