** *Block 2* **					
*Target and non-target religious group labels*	Christian or not Christian	Catholic or not Catholic	a member of the Church of Jesus Christ or not a member of the Church of Jesus Christ	Jewish or not Jewish	Muslim or not Muslim

Unaffiliated children in the US are shown the version of the protocol that corresponds to the religion with which they are likely most familiar (see main text for details). See main text for descriptions of network-wide guidelines for item selection. “L.D.S.” stands for “Latter-day Saints.”

As in other tasks, the range of religious and neutral properties included in this task is intended to vary across samples in order to preserve cultural and religious specificity and appropriateness, within certain limits intended to maintain a balanced level of standardization across samples. To achieve this, for each sample we include one religious property concerning an internal *belief state* that members of the target religious group are likely to hold, as well as a matched neutral belief that both members and non-members are equally likely to hold; one religious property concerning a *holiday* that members of the target religious group are likely to observe or celebrate, as well as a matched neutral holiday that both members and non-members are equally likely to celebrate; and (3) one religious property concerning a *prayer-like practice* (e.g., prayer, blessings, or other communication with the divine) that members of the target religious group are likely to engage in, as well as a matched neutral activity that both members and non-members are equally likely to engage in habitually.

The properties included in this task sometimes focus on the character individually (e.g., “Here is a kid who…”) and sometimes on the character’s family (e.g., “Here is a kid whose family…”), as deemed appropriate in a given setting. Research teams have been encouraged, but not required, to select religious properties that differentiate among salient religious groups in the local context (e.g., choosing a belief about Jesus rather than God in settings where Christians live alongside members of other monotheistic religions); the only strict requirement is that these properties should be salient aspects of religious identity and should be familiar and relevant to children, as confirmed by local informants (e.g., religious leaders, parents of young children).

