At the beginning of each block, the child is presented with a grayscale silhouette of character. The researcher introduces the character as an adult member of the target religious group who habitually violates a religious, moral, or conventional norm; see Table 5 for norms selected for each US sample. There is no visual depiction of the specific norm violation, and silhouettes are matched with stories at random. The child is then asked a series of questions about the norm in question, in a fixed order. First, the child is asked about the *permissibility* of the norm violation (“Is that okay or not okay?”) and is asked to explain their response (“Why is that [okay/not okay]?”). Second, the child is asked to rate the *severity* of the norm violation (“And how good/bad is it that…?”) on a three-point scale (“not good/bad,” “just a little bit good/bad,” or “very good/bad”). Third, the child is asked about the *alterability* of the norm by religious authorities; this is gauged by asking the child to reassess the permissibility and severity of the norm violation if a religious authority declared the norm violation to be okay (“What if [God/another religious authority] said that it was okay to…–then would it be okay for…? And how good/bad would that be?”). Fourth, the child is asked about the *scope* of the norm, i.e., whether it applies beyond the target religious group; this is gauged by asking the child to reassess the permissibility and severity of the norm violation if it were committed by a non-group member (“This is a man named Morgan. Morgan is not Muslim. Morgan …”). The child answers all of these questions for a single norm before proceeding to the next block, which features a different norm.

**Table 5 pone.0292755.t005:** Sample-specific item selection for the Norm Violations task (including the familiarity assessment at the end of the task), for the five religions included in US samples.

	Religion				
	*Protestantism*	*Catholicism*	*Church of Jesus Christ of L*.*D*.*S*.	*Judaism*	*Islam*

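### In the Catholic version, norms and a belief item shared with the Protestant version are judged against the narrower label 'Catholic', so label level is mixed into the scope and indicator contrasts

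*Protocol article*

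**What the plan says.** **Norm selection.** The guidelines after Table 5 require religious norms to separate the target group from other world religions and other high-level local groups. Norms may separate sub-groups too, but they are not "required to distinguish sub-groups within an overarching religion, e.g., Sunni vs. Shia; Catholic vs. Protestant".

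**Norms chosen.** In the Catholic column of Table 5 the first religious item reads "Character] is Catholic. [Character] never goes to church" and the second "Character] is Catholic. [Character] was never baptized". The Protestant column describes the same two behaviours with the label *Christian*. The familiarity rows of the two columns also match.

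**Scope question.** Norm Violations, Task design and procedure, defines the scope of a norm as "whether it applies beyond the target religious group; this is gauged by asking the child to reassess the permissibility and severity" when the violator is not a group member. The one printed example negates the target label (a man who is not Muslim).

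**Indicators.** In Table 3 the belief item "Here’s a kid who believes that Jesus died for our sins" stands in both the Protestant and the Catholic columns. The Block 2 response for the Catholic version is "Catholic or not Catholic"; for the Protestant version it is Christian or not. The Catholic holiday item, "Here’s a kid who goes to mass on Ash Wednesday", and the rosary item differ from their Protestant counterparts.

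**Analyses.** Hypotheses 1d and 2b use ratings of the non-member character, and also the change from the child's own rating of the member. Block 2 is tested by property type, property type x indicator type, and property type x age.

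**The concern.** Each rule is reasonable alone; the difficulty lies in the combination. Norms are required to be distinctive at the level of Christian against other religions, but in the Catholic version they are probed at the level of Catholic against everyone else, including other Christians. By the protocol's own Table 5, church attendance and baptism are also norms for Christians in general. Answering *not okay* for a non-Catholic can therefore reflect correct knowledge, yet it enters the analysis as extending a religious norm beyond the group. The same norms in the Protestant version do not have this ambiguity.

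Three readings are affected: the pooled tests of 1d and 2b; any Catholic-Protestant comparison of scope, where the Norm Violations planned analyses put the main interest in differences across groups; and, in Block 2, the comparison of belief with holiday and prayer items. If knowledge that other Christians hold the belief grows with age, the property type x age test in the Catholic version is also pulled against its hypothesis.

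**Working it through.** **1. Columns side by side**

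| Element | Protestant version | Catholic version | Shared? |
|---|---|---|---|
| Religious norm 1 | never attends church | never attends church | yes |
| Religious norm 2 | never baptized | never baptized | yes |
| Belief indicator | Jesus died for our sins | same sentence | yes |
| Holiday indicator | church on Easter | mass on Ash Wednesday | no |
| Prayer indicator | closing words in Jesus' name | rosary | no |
| Label negated in Block 2 | Christian | Catholic | level differs |
| Label negated in scope question | Christian (inferred) | Catholic (inferred) | level differs |

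Overlap is 2 of 2 religious norms and 1 of 3 religious indicators. The last row is inferred from three things: the printed Muslim example, the statement that the target group is matched across tasks, and the label given to the Table 5 characters.

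The Latter-day Saints prayer item is close to the Protestant one and is judged against the narrower label of church membership, so it has the same structure. That version's two norms (giving money to the church, coffee) are not the Protestant ones.

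**2. Effect on the planned contrasts**

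Take a child who says *not okay* for the member and for the non-member because other Christians share the norm. The non-member rating resembles that for a moral norm, and the change score is zero, as for a moral norm. Both planned analyses of scope therefore move against 1d and 2b, and the change score does not remove the problem.

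In Block 2, a child who knows the belief is shared may rate its holder less firmly Catholic. That lowers the religious-minus-neutral difference for belief but not for holiday or prayer.

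**3. Illustration of size (all inputs assumed)**

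The document gives no figure to reproduce. Let b be the share applying the norm to a non-member in the Protestant version, and k the share of Catholic-version children who say *not okay* because other Christians share the norm. The Catholic-version rate is b + k(1 - b), so the gap is k(1 - b).

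| b | k | Catholic rate | Gap | Chance p < 0.05, n = 75 per group | n = 100 per group |
|---|---|---|---|---|---|
| 0.30 | 0.1 | 0.37 | 0.07 | 15% | 18% |
| 0.30 | 0.3 | 0.51 | 0.21 | 75% | 86% |
| 0.30 | 0.5 | 0.65 | 0.35 | 99% | >99% |
| 0.20 | 0.3 | 0.44 | 0.24 | 89% | 96% |
| 0.50 | 0.3 | 0.65 | 0.15 | 46% | 57% |

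The sample sizes are the planned US minimum and maximum; the test is a two-sided comparison of two proportions at 0.05.

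With six equal samples, one of them on the Catholic version, the pooled rate moves by one sixth of the gap. For b = 0.30 that is 0.07/6 = 0.012, 0.21/6 = 0.035 and 0.35/6 = 0.058. Unaffiliated children given the Catholic version would raise this.

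For Block 2, if a share k drops d points on the four-point belief rating, the belief contrast in the Catholic version falls by k x d and the three-item average by k x d/3. With k = 0.3 and d = 1 to 3, that is 0.3 to 0.9 and 0.1 to 0.3 points.

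**The case against.** The strongest reply is that this is a disclosed design choice. Shared norms are expressly permitted, differentiating indicators are encouraged rather than required, label specificity follows local usage, and the Discussion warns that cross-sample comparisons must allow for version differences, naming Protestant and Catholic versions. All of that stands, so a reader who infers a breach of the protocol's own rule would be wrong. The general caution does not, however, say which contrasts are affected or what to do about them.

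A reader might also infer that children are marked wrong. The documents do not support that: neither task scores answers as right or wrong, and Block 2 asks only whether the belief draws higher ratings than a neutral one, which a shared Christian belief may still do. The issue is that such answers shift the planned contrasts.

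Third, the bias on 1d and 2b is conservative and comes from one of five versions, and comparisons across samples are labelled exploratory. This is correct and limits the consequence for the pooled tests. It does not protect the Catholic-Protestant comparison.

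Fourth, the *not Catholic* wording of the scope question is not printed in the article; the full scripts are in the online repository. The inference is strong but remains an inference.

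Finally, the Direct Questions task records whether a child self-identifies as Christian and as Catholic. That is a partial check on this knowledge, not a remedy.

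**Conclusion.** The point holds as a measurement ambiguity confined to particular items: both religious norms in the Catholic-version scope question, the Catholic belief pair in Block 2, and, as a matter to check, the Latter-day Saints prayer pair. For 1d and 2b it makes the pooled tests somewhat conservative. For a Catholic-Protestant scope comparison it can produce a difference without any real one. In Block 2, item overlap is confounded with indicator type.

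The size is unknown. The illustrative gaps should not be read as estimates: nothing in the document says how many children aged 4 to 10 think of other Christians when asked about a non-Catholic, or how that changes with age. The conclusion rests on the inferred scope label and on the protocol's own listing of the two norms in its Protestant (Christian) version.

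**What to change.** Three additions to the analysis, using data already being collected:

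1. Run the pooled scope tests of 1d and 2b with and without the Catholic-version religious-norm scope trials, including those from unaffiliated children given that version.
2. Run the Block 2 property type x indicator type and property type x age tests with and without the Catholic belief pair and the Latter-day Saints prayer pair.
3. State that Catholic-Protestant differences in scope will not be interpreted as group differences.

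The cost is fewer trials in the reduced analyses. With two religious norms per child, 75 to 100 Catholic-sample children account for 150 to 200 of 900 to 1,200 US religious-norm scope trials, plus those of any unaffiliated children on that version. In the reduced scope model these children contribute only moral and conventional trials, which should be said when it is reported.

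The outsider label should not be changed during Wave 1. Doing so would split the Catholic sample across two wordings near its stop date, and a non-Christian outsider alone would no longer test scope beyond the target group. For later waves, a separate non-Christian probe could be considered as an addition, not a replacement.
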